### Time course

We expect that the time course data will show significant divergences between the conditions after each verbal prompt. Based on our pilot data, we envision that after each prompt, infants in the Semantic Priming condition will exhibit increased proportion of looking to the target, which we predict to be above the chance level. In the Follow-up Control condition, infants’ looking behavior is likely to not be significantly affected by the verbal prompts because according to our hypothesis, they will have no particular expectations about the meaning of the novel word. It is, however, also possible that they will exhibit a weak preference for the target object (the object that is target in the Semantic Priming condition) based on their expectations about the next item shown given the relatedness of the three demonstrated objects. In the No Priming condition, infants have no basis to form any particular expectation about the object or the meaning of its label. For this reason, we expect that infants’ looking behavior will not be affects by the verbal prompts and remain around the chance level for the duration of the test trial.

#### Pilot data

The results of the pilot data analyses (*N* = 18) in the Semantic Priming condition reveal a significant looking preference for the target. Infants’ LT to the target image across 6 s was significantly above chance (50%), *M* = 64%, *SD* = 8%, *t*(17) = 5.5, *p* < .001. The time course data reflects infants’ reactions to verbal prompts: infants’ looking to the target increased after each mention of the target word (Fig 3). These data provide assurances that the task is well-suited to test 15-month-olds’ ability to learn novel word meanings from displaced reference and provides hints that infants might indeed be using semantic priming to infer such meanings.

**Fig 3 pone.0244968.g003:**
[figure not shown]
Time course of the pilot data (*N* = 18) in the semantic priming condition.

### Results and discussion

We reasoned that if 15-month-olds can establish novel word-object mappings from language alone, it would indicate that they *can resolve abstract verbal reference*. Alternatively, failure on this task will raise several possible interpretations. First, 15-month-old infants may be sensitive to semantic priming [29], but not sufficiently robust to support learning a novel word in the absence of its referent. Second, infants may fail to infer that there is an object behind the actor. If this is the case, further investigation will be necessary to clarify the presence of a hidden object. Third, it is possible that 15-month-olds can resolve abstract verbal reference, but that their exposure to the novel word during priming is insufficient for them to establish novel word-object mappings from displaced reference. These possibilities all warrant follow-up investigations, which will shed light on the development of infants’ inferential and representational capacities and their ability to use such capacities in word learning. We have designed such follow-up studies and will conduct them if 15-month-olds fail to learn the meanings of novel words in Experiment 1. However, based on the pilot data, we predict that these infants will succeed, which leads us to Experiment 2.

To be expanded when data collection and analyses are complete.

## Experiment 2

If the results of Experiment 1 suggest that at 15 months, infants successfully establish novel word-object mappings from language alone, then we will go on to identify entry points for this capacity. More specifically, we will focus on 12-month-old infants, whose command of representational [43–45], lexical [46], and communicative capacities [5,47] suggests that they may be able to successfully resolve abstract verbal reference. By at least by 12–13 months, naming profoundly influences infants’ learning. Applied consistently, words help infants form conceptual categories [45,48,49], as well as guide their attention to commonalities among and differences between individual exemplars [50]. Further, infants as young as 13-months-old rely on labels to infer non-visible properties and extend them to novel instances of a category, even when they are not especially perceptually similar to the learning exemplars [e.g., 51,52]. These early capacities lead us to hypothesize that provided with a large enough lexicon, 12-month-olds may successfully learn novel words from language input alone. Experiment 2 investigates this possibility.

Focusing on 12-month-olds, however, raises a new challenge. For our semantic priming manipulation to succeed, infants must comprehend at least 3 words from each semantic neighborhood under investigation (e.g., fruits, clothing, vehicles). Yet 12-month-olds’ existing lexicons are rather sparse: only 30% of 12-month-olds meet this lexical requirement [28]. To redress this limitation, we initiate an at-home vocabulary training phase designed to bolster infants’ lexical comprehension before they participate in the experiment proper.

### Method

#### Participants

Participants will be 72 infants (*N* = 24 per condition: Semantic Priming, No Priming, Follow-up Control) recruited from Chicagoland area. All recruitment and consent procedures will be identical to Experiment 1. Participants may be excluded and replaced due to fussiness, crying, or equipment failure.

Apparatus, stimuli, and data preparation will be identical to Experiment 1. All IVs, DVs, and analyses will also be the same as in Experiment 1, except that infants’ LT to the target on the familiar word knowledge test will be added to the main analyses.

#### Timeline

We intend to begin data collection as soon as the current registered report is granted *in-principle acceptance*. We expect that all data will be collected and analyzed within a calendar year from the completion of Experiment 1. The projected timeline to complete both proposed experiments is two calendar years from the *in-principle* acceptance date.

#### Procedure

The experimental procedure will be identical to Experiment 1 with one exception: before infants participate in the experiment proper, their parents will be enlisted to provide an at-home vocabulary training phase to bolster their infants’ lexical comprehension. Two weeks before their lab visit (or online participation on Lookit), participants’ parents will receive an online digital picture book containing 24 word-image pairs, including the 12 pairs featured in the Priming phase of the experiment proper. The order of word-image pairs will be randomized among participants. Parents will be asked to read their book at least once per day for 14 days, pointing to each picture and articulating its name. Before parents begin reading the book to their infants, they will view a video demonstration that will provide guidelines to reading this book to their infants and suggestions for establishing a daily reading routine (e.g., read before bedtime or after the nap, etc.). Moreover, parents will be contacted (email or text, as the parent prefers) every other day, reminding them to read the book to their infant. Parents will also be asked to fill out an online form daily (see S4 Appendix), reporting how engaged their infant was during the reading sessions. This at-home training should bolster infants’ lexical knowledge, permitting us to test their ability to learn words from displaced reference when they visit the lab.

When infants visit the lab (or participate in the study online via Lookit), we first test comprehension of the 12 words included in the experiment proper. On each of 12 trials, infants will see two images from their book—one that will be used in Priming (e.g., apple, a target) and another (e.g., spatula, a distractor). Following Bergelson and Swingley [2012; 53], infants will be prompted to look at the target (“Look, an apple!”). The proportion of LT to the target will be evaluated against chance (50%). It is possible that infants will fail to learn words used in Priming during the two-week exposure to picture-book reading. If this is the case, we will explore alternative methods of boosting infants’ word knowledge and consider alternative way of testing their ability to establish new word-object mappings from abstract reference.

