#### Participants

Seventy-two (*N* = 24 per condition) infants from the Chicago area will be recruited from the laboratory database. Infants will have no more than 15% exposure languages other than English. Caregivers will complete a MacArthur Short Form Vocabulary Checklist: Level II [Form A; 32], augmented with words used in the experiments but not included in the form (see S1 Appendix). They will also complete a demographic questionnaire about their education, employment, gender, and race (see S2 Appendix).

The number of participants was determined based on power analysis performed with G*Power 3.1 [33] for a repeated measures between-subject F-test with target effect size *f*^2^ = .1225 (medium; [34], *alpha* = .05, power = .8, number of groups (experimental conditions) = 3, number of trials = 4, and projected correlation between measurements = .5. We reasoned that compelling evidence would require at least a medium effect size of experimental condition. Based on these parameters, the required number of participants is 72. The planned analyses include Generalized Linear Mixed Model rather than an F-test. We used F-test-based effect size estimations for simplicity. The four test trials were treated as repeated measures.

Participants may be excluded and replaced due to fussiness, crying, or equipment failure. Further, because our Covid-19 Contingency Plan (see below) involves testing infants using Lookit–an online platform designed for developmental research–we expect a data loss rate of about 47–50% [35] due to infants’ crying or fussiness, parental interference, or technological issues. This, we anticipate that the total number of infants recruited could reach 140.

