#### Predictions

We expect that on the comprehension task that tests infants’ knowledge of the familiar 12 words, infants will exhibit excellent performance and look to the target images over 70% of the time over the course of the trial. In the experiment proper, if 12-month-olds can indeed establish a representation of word meaning from abstract verbal reference, they should successfully map the novel word to the unseen object, echoing the results of Experiment 1. We expect to observe a significant effect of Condition on both DVs–the overall proportion of LT to the target across 6 s and the time course of infants’ LT. We predict that the direction of differences will be the same as in Experiment 1. Further, if our hypothesis is correct, then infants’ performance on the comprehension test will be correlated with their success in the experiment proper. However, if despite vocabulary training, 12-month-olds fail to learn novel words, this will either suggest that these infants cannot yet resolve abstract verbal reference, or that their sensitivity to semantic priming is insufficiently robust to guide inferences about absent objects. Additional investigations will be required to distinguish between these possibilities.

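### Experiment 2: target looking above 50% does not show that 12-month-olds know the prime words the design requires, and the planned reading of a null leaves that explanation out

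*Protocol article*

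**What the plan says.** The opening of Experiment 2 sets a prerequisite for the priming manipulation: "infants must comprehend at least 3 words from each semantic neighborhood under investigation". It adds that "only 30% of 12-month-olds meet this lexical requirement", and introduces two weeks of picture-book reading at home to overcome this.

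Under Procedure (Experiment 2), comprehension of the 12 prime words is tested by looking at the visit or online session, after the reading period and before the main task. The criterion is: "The proportion of LT to the target will be evaluated against chance (50"%). If infants turn out not to have learned the words, the authors will look for other ways to raise word knowledge.

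Under Participants (Experiment 2), "Participants will be 72 infants", 24 per condition, and looking on the comprehension test is added to the main analyses. Predictions (Experiment 2) expects looking above 70% on that test and a correlation with success in the main task. It then fixes the reading of a null: "if despite vocabulary training, 12-month-olds fail to learn novel words, this will either suggest that these infants cannot yet resolve abstract verbal reference", or else that sensitivity to priming is too weak. Further studies are promised to separate those two readings.

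**The concern.** The prerequisite is a property of each infant in each neighborhood. The check compares looking with chance. These are different questions: a sample in which a minority knows the words well and the rest know none of them can average clearly above 50%. By the plan's own 30% figure, 50% is not even what one would expect from an untrained sample. The 70% figure is a prediction and plays no part in the rule.

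At stake is the meaning of a null at 12 months. If the check passes while most infants lack the primes, the main comparison is diluted for lexical reasons. The plan then offers two readings, and neither is missing word knowledge, although the opening of Experiment 2 names sparse lexicons as the particular challenge at this age.

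**Working it through.** **The plan's own figures.** The plan gives no sample size or power for the comprehension check. Its one calculation, under Participants (Experiment 1), concerns the main comparison ("target effect size *f*^2^ = .1225", "alpha* = .05, power = .8", "number of groups (experimental conditions) = 3, number of trials = 4, and projected correlation between measurements = .5") and states 72 infants. With noncentrality f²·N·m/(1+(m−1)ρ) and N−3 error degrees of freedom, those inputs give N = 54 (power .814), and power .919 at 72. So 72 is not reproduced. That does not affect this point, which takes 72 as the planned number.

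**Inputs for the check**
- N = 72; alpha .05, taken as two-sided (the plan does not give the sidedness of this test).
- Share already meeting the requirement: 30%, from the plan.
- No training effect: the other 70% look 50% to target (assumption).
- Knowers' looking k: 70%, 65% or 60% (assumption; 70% is the plan's expectation for trained infants).
- SD between infants: not given for this task. The 15-month pilot prints 8 points. Its t(17) = 5.5 with mean 64% implies 14·√18/5.5 = 10.8 points, whereas SD 8 would give t = 14/(8/√18) = 7.4. Range used: 8, 10.8 and 15.

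**How low a mean passes.** Threshold = 50 + 1.994·SD/√72, which is 51.9% (SD 8), 52.5% (SD 10.8) or 53.5% (SD 15).

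**Chance of passing with no training effect.** Mean = 50 + 0.3(k − 50). Total SD s = √(SD² + 0.21(k − 50)²). Noncentrality = (mean − 50)·√72/s. Example with k = 70 and SD 8: mean 56, s = √(64 + 84) = 12.17, noncentrality 6·8.485/12.17 = 4.18, pass probability .985.

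| Knowers look | Group mean | SD 8 | SD 10.8 | SD 15 |
|---|---|---|---|---|
| 70% | 56.0% | .985 | .94 | .82 |
| 65% | 54.5% | .95 | .84 | .63 |
| 60% | 53.0% | .78 | .57 | .36 |

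Simulating the mixture directly agrees within .01 (.99 in the first cell). With knowers at only 55% the probabilities are .33, .21 and .13.

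**Consequence for the main test.** Suppose the pilot's 14-point effect carries over, No Priming sits at 50%, and only 30% of infants can be primed. The effect becomes 0.3 × 14 = 4.2 points. The Semantic Priming SD becomes √(SD² + 0.21·14²), which is averaged with the No Priming variance. For 24 against 24 (two-sided t, 46 df), power falls from 1.00 to .34 (SD 8), from .99 to .23 (SD 10.8) and from .89 to .15 (SD 15). With SD 8: pooled SD 9.2, noncentrality 4.2/(9.2·√(2/24)) = 1.58.

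**The case against.** Several stronger readings are tempting, and the document does not support them.

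*A reader might infer that word knowledge is otherwise ignored.* It is not. Comprehension scores enter the main analyses, a correlation with success is predicted, and Experiment 1's preliminary test of vocabulary scores carries over. These are real but partial guards. A main effect of comprehension does not ask whether the Condition effect depends on knowing the primes, and nothing links these analyses to the reading of a null.

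*A reader might infer that nothing is measured before training.* The looking test comes after it, but the timing of the caregiver checklist, which is augmented with the experiment's words, is not stated.

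*A reader might want a before-and-after contrast.* Experiment 2 asks what infants who know the primes can do, so knowledge at test is what matters and its source is secondary.

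*A reader might infer that the check will nearly always pass.* That depends on unstated quantities: at 60% looking and SD 15 it passes about one time in three. The 70% is an expectation for trained infants, the SD comes from another age and task, and the 30% is a norm that need not refer to these 12 words. A group-level test is also only the natural reading of the sentence.

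*A reader might infer that a null will be misread.* Failure to learn the primes is foreseen under Procedure, and the readings under Predictions are tentative. But the Procedure branch depends on the check detecting that failure, and the promised follow-up separates only the two listed readings.

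**Conclusion.** The point holds in a limited form. Exceeding 50% cannot establish three known words per neighborhood in each infant, whatever the SD. How often the check would pass with no training effect depends on assumptions: about .99 to .82 with knowers at 70%, .95 to .63 at 65% and .78 to .36 at 60%, for SDs of 8 to 15 points, 72 infants and non-knowers at exactly 50%. In that situation the main contrast would have power of roughly .15 to .34 if the pilot effect applied only to knowers. Since insufficient prime-word knowledge is not a listed reading of a null, a 12-month null could be attributed to the wrong cause. It is worth correcting before data collection. It does not invalidate the design, and a positive result is not threatened by it.

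**What to change.** 1. Use the 12 comprehension trials and the augmented caregiver checklist to report the share of infants who meet the three-words-per-neighborhood requirement at test, under a scoring rule fixed in advance. Set it beside the plan's 30%, and the group mean beside the plan's 70%. Do not treat a result above 50% as success in itself. State that the checklist is completed at the test session in Experiment 2.
2. Add a Condition-by-comprehension term to the main model as a supporting analysis.
3. Under Predictions (Experiment 2), list insufficient prime-word knowledge as a third reading of a null. Draw the conclusion that 12-month-olds cannot yet resolve abstract verbal reference only if the prerequisite is shown to be met; otherwise state that it was not established.

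Giving the checklist when the picture book is sent as well is optional, and would serve only to show that training worked.

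Cost: wording and a little more analysis, with no extra infants or visits. The limits should be stated openly. Infant-level scores rest on three looking trials per neighborhood plus caregiver report, and the interaction will be imprecise. If training does nothing, about 0.3 × 72 ≈ 22 infants would qualify, roughly 7 per condition, so a qualifying subset could support little on its own. The conclusion from a null becomes more cautious.

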#### Stimulus selection and design

We used vocabulary norms [36] to select the visual and linguistic materials. For the familiar objects presented in the Priming phase, we selected objects whose names are understood by at least 60% of 15-month-olds (nouns: apple, banana, orange, jacket, sock, hat, truck, car, bus, cat, dog, horse). For the novel objects presented during Test, we (a) selected objects whose names infants do not understand (e.g., rare tropical fruits, exotic animals), and (b) chose pairs of objects from distinct semantic neighborhoods (e.g., papaya vs aardvark).

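### Experiment 2's looking-based comprehension check compares raw looking with 50%, so a group-level picture preference could pass as word knowledge or hide it

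*Protocol article*

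**What the plan says.** The Procedure section of Experiment 2 describes "an online digital picture book containing 24 word-image pairs, including the 12 pairs featured in the Priming phase of the experiment proper". After 14 days of reading, the article says "we first test comprehension of the 12 words included in the experiment proper". The layout is stated: "On each of 12 trials, infants will see two images from their book", namely "one that will be used in Priming (e.g., apple, a target) and another (e.g., spatula, a distractor"). The Priming nouns are listed under Stimulus selection and design ("nouns: apple, banana, orange, jacket, sock, hat, truck, car, bus, cat, dog, horse"), and spatula is not among them.

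The score and benchmark are also stated: "The proportion of LT to the target will be evaluated against chance (50"%). The Predictions section expects infants to "look to the target images over 70% of the time over the course of the trial", which describes looking over the whole trial.

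The result has three uses. If infants fail to learn the words, the Procedure section says other ways of raising word knowledge will be explored. The Participants section says that infants' "LT to the target on the familiar word knowledge test will be added to the main analyses". The Predictions section expects the score to correlate with success in the experiment proper.

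**The concern.** Only the 12 Priming words are tested, one per trial, so a Priming picture is the target on every trial. On the plain reading, the distractors come from the other 12 pictures in the book. Which picture is shown and which role it plays are then confounded. An infant who knows none of the words but prefers to look at animals, vehicles, fruit or clothing rather than kitchen utensils would score above 50%. An infant with the opposite preference could know the words and score at or below 50%. Balancing left and right positions does not help, because the confound is between picture and role.

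The article treats baseline preference as a rival explanation in the main task, where the No Priming condition is the safeguard. The comprehension check has no counterpart, since all three conditions receive the same training.

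Two things are at stake. One is the decision that training worked, which matters because the article says only 30% of 12-month-olds otherwise meet the lexical requirement. The other is the reading of a null in Experiment 2: the Predictions section offers two explanations after training, and neither is that the prime words were not known.

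**Working it through.** The plan gives no power figure for this check, so there is none to reproduce. The question is how small a picture preference would produce a significant result with no word knowledge.

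**Inputs**
- N = 72 (Experiment 2, Participants).
- Two-sided alpha .05 and a one-sample t-test on infant means. Alpha .05 is given for the main power analysis; the form of the test is assumed.
- SD of an infant's mean proportion. None is given for this check. The pilot (four-trial task, 15-month-olds) reports 8 points. The pilot's mean of 64% and t(17) = 5.5 imply instead 14 × √18 / 5.5 = 10.8 points. The upper value of 15 is an assumption, allowing for younger infants and webcam coding.
- Mean preference b for the target pictures, in points above 50. Not given; assumed.

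**Smallest observed preference that reaches p < .05**

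b_min = t(.975, 71) × SD / √72, with t = 1.994 and √72 = 8.485.
- SD 8: 1.994 × 8 / 8.485 = 1.9 points
- SD 10.8: 1.994 × 10.8 / 8.485 = 2.5 points
- SD 15: 1.994 × 15 / 8.485 = 3.5 points

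If each group of 24 were tested separately, the values would be 3.4 points (SD 8) to 6.3 points (SD 15).

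**Chance of an above-chance result with no word knowledge**

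Upper-tail rejection from the noncentral t with 71 df and noncentrality b / (SD / √72):

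| Mean preference b | SD 8 | SD 10.8 | SD 15 |
|---|---|---|---|
| 0 | 2.5% | 2.5% | 2.5% |
| 2 points | 55% | 34% | 20% |
| 3 points | 88% | 64% | 39% |
| 4 points | 99% | 87% | 61% |
| 5 points | 99.9% | 97% | 80% |

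By symmetry, the same preference toward the distractors would pull the score down by b and mask knowledge worth b points.

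**Simulation with fixed pairs**

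Twelve fixed pairs, 72 infants and no word knowledge were simulated 2,000 times per setting, with assumed SDs of 5 points between infants, 20 between trials and 10 between pair preferences. For a mean tilt of 0, 2, 3 or 5 points, the stated test declared above-chance looking in 29%, 52%, 65% and 86% of studies. Even with no average tilt, 12 pairs rarely balance exactly: the SD of their mean preference is 10 / √12 = 2.9 points. Subtracting a pre-naming baseline gave 2.0% to 3.2%. Exchanging target and distractor roles within pairs across infants gave 1.5% to 1.9%. The nominal upper tail is 2.5%.

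**Why reciprocal pairs remove the preference**

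Take pictures A and B, with a preference d for A. With no word knowledge, looking to A is 50 + d when A is named and 50 + d when B is named. The difference is 0 whatever d is. In general the pair score is P(A | A named) − P(A | B named) = P(A | A named) + P(B | B named) − 1. It is the same number whichever picture is taken as A, so 12 pictures give six scores.

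**The case against.** Several points on the other side stand.

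- **A second measure exists.** Caregivers complete a vocabulary checklist augmented with words used in the experiments (Experiment 1, Participants). A reader might infer that the looking test is the only evidence on these words. It is not, although the checklist is parent-reported and its timing relative to training is not stated.
- **The main comparison is not biased.** A reader might infer that putting the score into the main analyses contaminates the condition effect. Condition is assigned at random, and a preference shared by all infants shifts the covariate by a constant, which changes neither its slope nor the predicted correlation. Preferences that differ between infants add noise.
- **A null is not given one fixed meaning.** A reader might infer that it would be reported as inability to resolve abstract reference. The Predictions section gives that or weak sensitivity to priming, and says more work is needed to tell them apart. Unknown prime words are still missing from the list.
- **The fixed distractor role is the plain reading, not an explicit rule.** It rests on the contrast in the wording and one example. The text does not say that a Priming picture can never be a distractor.
- **Both pictures come from the same book**, so unequal familiarity is limited. Unequal appeal is not.
- **Failure to learn is not defined as p ≥ .05.** A score of 52 to 54% would visibly miss the expected 70%. That figure is a prediction, however, not a pass mark.

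That an article leaves pairing lists to a fuller document is a weaker objection. The type of pairing, the score and the benchmark are stated here, and together they do not isolate word knowledge. The prompting follows a cited study, but no correction for preference is carried into the text.

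**Conclusion.** The concern holds for the looking-based comprehension check. As written, 50% is not the value expected without word knowledge unless the Priming and distractor pictures happen to be equally attractive. At N = 72, a mean preference of about 1.9 points (SD 8), 2.5 points (SD 10.8) or 3.5 points (SD 15) is enough for significance with no word known, and the opposite preference would conceal learning. Only the SD of 8 is reported, and for a different task and age group. The size and direction of any preference are assumptions, so this shows that the check is vulnerable, not that it will mislead.

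The damage is limited to judging whether training worked and how a null in Experiment 2 is read. A reader might want to call this a fatal flaw in Experiment 2. The documents do not support that, because the randomised contrast is unaffected and the checklist gives a second view of word knowledge. Severity is moderate.

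**What to change.** Keep 12 trials. Form six reciprocal pairs from the 12 Priming pictures, each pair crossing two neighborhoods (for example apple with dog), and name each picture once. The 12 trials hold 12 × 2 = 24 picture slots, so each picture appears once as target and once as distractor. Score each pair as looking to a picture when it is named minus looking to it when it is the distractor. Use only pairs in which both trials meet the 1-second looking rule, and test the infant mean against 0. Randomise which picture of a pair is named first, so that any change in interest on second viewing averages out.

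If the existing distractors are kept, show each pair silently before naming, score post-naming minus pre-naming looking within the trial, and test that change against 0 in place of the comparison with 50%.

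Whichever score is chosen should also be the one added to the main analyses and used for the predicted correlation. It would help to list unknown prime words among the explanations of a null.

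Cost: neither version needs more infants or more trials. Reciprocal pairing gives six pair-level scores instead of twelve word-level scores, so knowing one word of a pair credits the pair. It also shows each Priming picture twice and loses a pair when either trial is invalid. The baseline version adds a short silent interval to each trial, a real cost given the article's own worry about exceeding infants' attention.
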